#### Secondary outcome

The secondary outcome will encompass changes in motor symptom scales such as the third part of the Movement Disorders-Unified Parkinson’s Disease Rating Scale (MDS-UPDRS III) [49], Mini-balance evaluation systems test (Mini-BES Test) [50], and 6-min walking test (6MWT) [51] from T0 to T1, T2, T3, and T4. Additionally, alterations in non-motor symptom scales such as non-motor symptoms scale (NMSS) [52], Montreal cognitive assessment (MoCA) [53], and Hamilton depression scale (HAMD) [54] from T0 to T2, T3, and T4 will be evaluated.

MDS-UPDRS III comprises of 18 items designed to evaluate motor function in individuals with Parkinson’s disease (PWP). The Chinese version of the MDS-UPDRS III demonstrates excellent reliability and validity, exhibiting a strong correlation with the conventional UPDRS [55].Mini-BES test is utilized for assessing gait and postural stability. This scale has demonstrated excellent inter-rater reliability (intraclass correlation coefficient (ICC) > 0.95) as well as high test-retest reliability (ICC > 0.95) [56].6MWT measures the distance that a patient can quickly walk on a flat, hard surface within 6 min. We used the validated Chinese version which has shown a very high inter-rater correlation coefficient (ICC = 0:99) [57].NMSS allows quantitative evaluation of NMS of PD. The Chinese version of the NMSS can be considered a comprehensive, useful measure for NMS evaluation in Chinese PWP (Cronbach’s coefficient = 0.89, ICC = 0.99) [58].MoCA is a screening tool for mild cognitive impairment. The reliability of the Chinese version of MoCA has been proven in the clinic [59].HAMD will be utilized for the evaluation of a patient’s anxiety and depression levels. Its Chinese version has been empirically validated as a reliable and valid assessment tool [60].

#### Mechanism research

The changes in brain plasticity before and after rehabilitation intervention will be detected using Electroencephalogram (EEG) and fMRI.

##### Electrophysiological recordings

The EEG acquisition will be performed using a 64-lead EEG cap (model waveguard™ original 64, Netherlands) to facilitate real-time recording of EEG signals [61]. Electrodes will be positioned according to the international standard 10/20 system, with bilateral ear mastoids serving as reference electrodes. The sampling frequency will be set at 1000 Hz, and band-pass filtering between 1 and 30 Hz will be implemented. Additionally, efforts will be made to maintain electrode impedance below 10kΩ in order to minimize interferences during signal acquisition [62]. Subsequently, the acquired data will be stored in a computer for offline analysis.

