## Abstract

**Background:**

The neural cells in the brains of patients with Parkinson’s disease (PWP) display aberrant synchronized oscillatory activity within the beta frequency range. Additionally, enhanced gamma oscillations may serve as a compensatory mechanism for motor inhibition mediated by beta activity and also reinstate plasticity in the primary motor cortex affected by Parkinson’s disease. Transcranial alternating current stimulation (tACS) can synchronize endogenous oscillations with exogenous rhythms, thereby modulating cortical activity. The objective of this study is to investigate whether the addition of tACS to multidisciplinary intensive rehabilitation treatment (MIRT) can improve symptoms of PWP so as to enhance the quality of life in individuals with Parkinson’s disease based on the central-peripheral-central theory.

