## Introduction

### Background and rationale {6a}

Parkinson’s disease (PD) is a common neurodegenerative disease whose clinical manifestations include motor and non-motor symptoms [1]. Motor symptoms comprise resting tremor, bradykinesia, gait disturbance, and myotonia. Non-motor symptoms encompass cognitive dysfunction, sensory abnormalities, depression, anxiety, and autonomic dysfunction [2–4]. These symptoms have a significant impact on the quality of life of patients and result in substantial medical expenses [5, 6]. Neuronal oscillations in the brain play a key role in the pathophysiology of PD. Specific frequency patterns can control communication and network resonance between brain regions, and rapid pathological neuronal synchronization in PD may be a causative factor for motor and non-motor disorders [7, 8]. Abnormal synchronized beta oscillatory activity has been observed at multiple levels within the basal ganglia network in both people with Parkinson’s disease and animal models [9, 10]. The beta activity is associated with symptoms of Parkinson’s disease, such as rigidity and bradykinesia, and can be modulated by medication and deep brain stimulation (DBS). Suppression of beta power is also correlated with improvement in dyskinesia. In humans undergoing invasive recordings, both levodopa and therapeutic DBS have demonstrated the ability to decrease oscillatory synchronization within the beta range (13–30 Hz), while simultaneously promoting oscillatory synchronization within the gamma range (60–90 Hz) across multiple structures within the motor network [11–14]. The gamma band activity is generally considered to have a prokinetic effect, serving as a compensatory mechanism for the akinetic role played by beta activity [15, 16]. Increased gamma power has been observed at the initiation of exercise [17], during exercise [18], and during motor imagery [19]. Studies have demonstrated that cortical gamma oscillations play a beneficial role in modulating the long-term potentiation-like plasticity of M1 in Parkinson’s disease and improve motor symptoms in PWP [20, 21].

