Transcranial alternating current stimulation (tACS), a non-invasive stimulation technique, is capable of modulating cortical activity by manipulating and entraining intrinsic oscillations through the injection of sinusoidal alternating current from the scalp, with the endogenous oscillations during entrainment synchronized with the extrinsic rhythmic stimulation [22, 23]. The extracellular application of alternating current (AC) electric field in tACS modulates neuronal transmembrane potentials at the cellular level, inducing sinusoidal changes. Even small polarizations of the cell membrane can significantly impact the firing rate of active neurons, while AC stimulation effects can be further amplified by neuronal networks [24, 25]. In recent years, mounting evidence suggests that tACS can modulate cortical rhythms by entraining endogenous oscillations and promote neuroplasticity in multiple brain regions, thereby enhancing motor function and alleviating non-motor symptoms in individuals with PWP [21, 26–29]. For security reasons, previous studies on the application of tACS in PWP have primarily focused on utilizing weak currents below 2 mA. Although these studies have demonstrated some efficacy in improving bradykinesia, tremor, and cognition among PWP [27, 30, 31], they have generally employed low energy levels and limited cortical region stimulation through single stimuli. Furthermore, the conclusions regarding long-term effects have been inconsistent [32]. Several recent studies have shown that high-intensity transcranial alternating current stimulation (Hi-tACS) with parameters of 77.5 Hz (gamma band) and 15 mA may be more potent inducers of certain deep brain regions and have been shown to be safe. The delivery of a current with a frequency of 77.5 Hz through electrodes placed on the forehead and mastoid areas has been reported to modulate beta-endorphin and neurotransmitter levels in the cerebrospinal fluid, brainstem, hypothalamus, and cortex [33, 34]. It has demonstrated efficacy in ameliorating chronic primary insomnia, refractory epilepsy, as well as anxiety and depression, while maintaining a proven safety profile [35–37]. However, the effectiveness and neurobiological mechanisms of Hi-tACS in improving motor and non-motor functions in PWP have not been investigated. It is crucial to explore the role of Hi-tACS as a large alternating current in Parkinson’s disease in terms of motor and non-motor symptoms, and quality of life.

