#### tACS + MIRT group and sham-tACS + MIRT group

During each treatment session, patients will receive tACS or sham tACS stimulation for 40 min twice a day. The treatment duration was standardized for each day (40 min per session, twice daily for 10 days, totaling 20 sessions). Patients will receive a 10-day MIRT program based on tACS treatment, which includes four distinct rehabilitation exercises per day with each session lasting 30–60 min.

Participants were comfortably seated on reclining chairs to receive FDA-approved tACS from Nexalin Technology, Inc. The administration of tACS was carried out by trained medical professionals following standardized instructions. This trial utilized two tACS devices, one sham and one active, which were identical in terms of size, color, appearance, weight, and odor. Each participant was consistently assigned to the same device throughout the entire intervention.

Patients were instructed to consume water prior to the intervention, maintain a state of relaxation or even sleep, and minimize communication with medical personnel. Three Nexalin conductive electrodes were positioned above the head according to the 10/20 international placement system, with a 4.45 × 9.53 cm electrode placed on the forehead corresponding to Fpz, Fp1, and Fp2. Two 3.18 × 3.81 cm electrodes were placed on each side in the mastoid region. The tACS stimulation waveform consisted of ramp-up and ramp-down periods lasting for 180 s and 12 s respectively. It was a square wave with an average amplitude of 15 mA and was equally distributed from the frontal region to the mastoid areas (amplitudes are reported as zero-to-peak). All participants received a total of twenty sessions involving either true or sham stimulation at a frequency of 77.5 Hz and intensity of 15 mA, respectively. Sham tACS had no active stimulation.

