### Methods for additional analyses (e.g., subgroup analyses) {20b}

In case of baseline differences between the 2 groups (tACS + MIRT and sham-tACS + MIRT), statistical analyses will be adjusted to take into account specific variables that may have influenced the results for subgroup analysis (e.g., LEDD, illness duration, and age). The post hoc analyses will also be performed with Bonferroni corrected *t*-tests to examine the improvements in all outcome variables through comparisons across different assessment time points. Additionally, distinct exploratory analyses will be conducted for EEG and functional MRI data in order to gain a more comprehensive understanding of the impact of tACS intervention on brain plasticity.

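### The 1–30 Hz EEG band-pass leaves out the protocol's entire gamma range, so the EEG as specified cannot show a gamma after-effect; beta stays measurable

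*Protocol article*

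**What the plan says.** Under Outcomes {12}, Mechanism research, Electrophysiological recordings, the article sets the EEG acquisition: "The sampling frequency will be set at 1000 Hz, and band-pass filtering between 1 and 30 Hz will be implemented". The same paragraph then gives an impedance target and says that the data are stored for later offline analysis. Statistical methods {20a} names MATLAB and EEGLAB for that offline step and gives no second band. Plans for assessment and collection of outcomes {18a} places EEG at T0 and T1.

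The stimulation is described in the intervention section: "All participants received a total of twenty sessions involving either true or sham stimulation at a frequency of 77.5 Hz". Background and rationale {6a} presents this kind of stimulation "with parameters of 77.5 Hz (gamma band) and 15 mA". The same section says that levodopa and deep brain stimulation "decrease oscillatory synchronization within the beta range (13–30 Hz") while "promoting oscillatory synchronization within the gamma range (60–90 Hz) across multiple structures within the motor network". The abstract puts the argument briefly: "enhanced gamma oscillations may serve as a compensatory mechanism for motor inhibition mediated by beta activity".

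On the role of the EEG, {20b} says that "distinct exploratory analyses will be conducted for EEG and functional MRI data in order to gain a more comprehensive understanding", and the abstract lists the mechanistic studies as tertiary outcomes.

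**The concern.** Gamma is one of the two bands on which the rationale rests. The trial stimulates at a gamma frequency and argues that enhanced gamma offsets beta-mediated motor inhibition. EEG is the only electrophysiological measure described. A filter that stops at 30 Hz removes the frequencies where a gamma change would appear, in both arms and at both visits. The EEG could then neither support nor contradict that part of the argument.

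Timing also matters. Trial status reports the first patient in October 2023 and completion expected by the end of 2024. If the filter acts before storage, each recording made this way lacks usable gamma data, and the loss cannot be repaired afterwards.

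**Working it through.** **Inputs, all from the protocol article**
- Pass-band 1–30 Hz, sampling 1000 Hz (Electrophysiological recordings).
- Stimulation frequency 77.5 Hz (intervention section), labelled gamma in {6a}.
- Gamma 60–90 Hz and beta 13–30 Hz ({6a}); the Discussion gives beta as 15–30 Hz.

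The pass-band is a specification, so there is no calculated figure of the plan to reproduce.

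**Step 1: overlap of bands.** Overlap = max(0, min of the upper limits − max of the lower limits).
- Gamma: min(30, 90) − max(1, 60) = 30 − 60 = −30, so the overlap is 0 of 30 Hz.
- Beta, {6a} range: 30 − 13 = 17 of 17 Hz.
- Beta, Discussion range: 30 − 15 = 15 of 15 Hz.

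**Step 2: distance of the stimulation frequency from the cut-off.** 77.5 − 30 = 47.5 Hz above it; 77.5 / 30 = 2.6 times its value.

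**Step 3: is the sampling rate the limit?** Nyquist frequency = 1000 / 2 = 500 Hz, well above 90 Hz. The 30 Hz cut-off is the limit.

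**Step 4: how much gamma might leak through?** The article gives neither filter type nor order. As an assumption, take a 1–30 Hz Butterworth band-pass at 1000 Hz sampling with design order 2, 4 or 8. Gain in dB:

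| Frequency | Order 2 | Order 4 | Order 8 |
|---|---|---|---|
| 25 Hz | −1.6 | −0.8 | −0.2 |
| 30 Hz | −3.0 | −3.0 | −3.0 |
| 60 Hz | −12.9 | −25.3 | −50.6 |
| 77.5 Hz | −17.4 | −34.6 | −69.1 |
| 90 Hz | −20.1 | −40.1 | −80.1 |

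A simple low-pass formula, 10·log10(1 + (77.5/30)^(2·order)), gives similar losses at 77.5 Hz: 16.6, 33.0 and 65.9 dB. Under these assumptions gamma is strongly attenuated, while beta loses at most 1.6 dB from 13 to 25 Hz and 3 dB at its upper edge. The conclusion rests on Steps 1 to 3, which need no assumption about the filter. Step 4 only shows scale.

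**The case against.** The strongest case on the other side has five parts.

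1. **Beta is as much part of the mechanism as gamma.** The abstract opens with aberrant beta synchrony, and {6a} links beta to rigidity and bradykinesia. Beta lies wholly inside the pass-band. This stands. A reader might infer that the EEG cannot test the trial's mechanism at all; the article does not support that.

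2. **The objectives do not promise gamma power.** The secondary objective speaks of functional connectivity and biomarkers of neuroplasticity, and the Discussion ties the goal to MRI techniques. This stands as well. The filter does not make a stated objective unreachable; it leaves part of the rationale unexamined.

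3. **EEG at T0 and T1 would not capture entrainment under any filter.** {6a} describes synchronization while stimulation is running, whereas the recordings come before and after the intervention. This stands: only an after-effect in gamma is at issue.

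4. **Filtering before storage is not established.** The order of the sentences suggests it, but the text does not say whether the filter acts in the recorder or later, and 1000 Hz sampling is compatible with wide-band raw files. Permanent loss of gamma is therefore a possibility and not a finding.

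5. **The outcome is tertiary and exploratory**, and a fixed filter applied at both visits and in both arms does not bias the beta comparison. This stands and lowers the severity.

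The mismatch itself survives. It is not a detail left to a fuller document: the article states the filter, and the stated band excludes the gamma range that the article itself gives.

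**Conclusion.** The point holds for gamma only. As specified, the EEG excludes all of the 60–90 Hz range and the 77.5 Hz stimulation frequency, so it cannot show a gamma after-effect from T0 to T1. Beta at 13–30 Hz and connectivity below 30 Hz remain measurable. PDQ-39, the secondary clinical outcomes and the sample size are not affected.

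Severity is minor to moderate, because the outcome is tertiary and exploratory. The conclusion assumes that the stated band-pass applies to the data that are analysed. If unfiltered 1000 Hz files are stored, gamma can be recovered and the remedy is a change to the offline processing. If the filter acts before storage, gamma is lost for the patients already recorded. The article does not say which is the case.

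**What to change.** In Electrophysiological recordings (Mechanism research, under Outcomes {12}):
- Record and store wide-band EEG at the stated 1000 Hz sampling, and apply filtering offline only.
- Set the upper analysis cut-off to at least 90 Hz, with line-noise removal, so that gamma can be analysed alongside beta as an exploratory measure.
- For patients already recorded, check whether unfiltered files exist. If the 1–30 Hz filter was applied before storage, state in the report that gamma cannot be assessed in those patients.

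The cost is a recorder or processing setting and a short protocol edit, since the sampling rate already supports the wider band. The downside is that scalp gamma carries more muscle artefact, so artefact rejection has to be planned and a gamma result read with caution.

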##### fMRI protocol

Structural 3D T1-weighted and rs-fMRI data were collected using a 3.0t MRI scanner (GE SIGNA Pioneer) [63, 64]. The imaging dataset included T1-weighted, T2-weighted, fluid-attenuated inversion recovery (FLAIR), and T2-star weighted angiography magnetic resonance images. A total of 240 volumes of rs-fMRI data were acquired. Additional file 2 provides the parameter settings for each MRI sequence. Participants will be instructed to close their eyes and achieve a state of relaxation while maintaining wakefulness.

### Participant timeline {13}

The participant timeline is shown in Fig. 2.

### Sample size {14}

PASS11 software was used to calculate the sample size. According to the previous literature [65, 66], which includes the results of PDQ-39 in individuals with Parkinson’s disease, and in combination with this experiment, we designed a ratio of 1:1 between the tACS + MIRT group and Sham-tACS + MIRT group. The statistical power was set at 0.9, with a significance level (α) of 0.05. Based on these parameters, the required sample size for each group was calculated as 27. Considering an attrition rate of 10%, it was determined that each group would need a total of 30 patients, resulting in a combined total of 60 patients.

### Recruitment {15}

Recruitment commenced on June 1, 2023, and concluded on December 31, 2023, or upon reaching the required number of patients, whichever transpired first. In the event that there is an insufficient number of registrations prior to the deadline, we will submit an extension application. Participant recruitment encompassed two strategies: The initial step involves referring patients who visit the outpatient clinic at Beijing Rehabilitation Hospital to project researchers for recruitment purposes. The recruitment notices were additionally disseminated through the hospital’s official website and various other online platforms, facilitating interested patients to conveniently schedule appointments online. Patients with confirmed appointments underwent initial telephone screening conducted by a rehabilitation physician to assess their eligibility prior to undergoing on-site evaluation at the outpatient clinic. Ultimately, eligible participants who provided written informed consent were randomized and received treatment.

## Assignment of interventions: allocation

### Sequence generation {16a}

The randomization of patients in a 1:1 ratio will be conducted by an independent researcher who is not involved in the assessments or stimulation. This researcher will be solely responsible for dispensing randomization numbers to patients in the order of enrollment throughout the trial. We will utilize the complete randomization function of SPSS 27.0 statistical software (IBM, Chicago, IL, USA) to generate a table of random numbers, and the SPSS Visual Binning function has been integrated into its system. The process of randomization will be overseen by a blinded worker from DMC who will have exclusive authority over managing the electronic coding for assigning individuals. The process will ensure complete automation without any human intervention and will remain entirely undisclosed to both study investigators and prospective participants until the assignment of study groups. This document will be entrusted to Beijing Rehabilitation Hospital, Capital Medical University for secure storage.

### Concealment mechanism {16b}

The coding group for the assignment concealment process will be placed in a sealed envelope, which will be labeled with each participant’s code and securely held by the staff responsible for randomization. The envelopes will only be opened during tACS or sham-tACS sessions. To ensure proper blinding, participants will receive a password that will remain concealed during allocation by an independent staff member responsible for randomization. The tACS experimenter, who administers the intervention, will also remain unaware of the group assignments. Both the tACS and sham-tACS devices will have identical appearances and be marked as either A or B. Additionally, a DMC staff member responsible for randomization will inform the tACS experimenter to use either device A or B.

### Implementation {16c}

The sealed envelopes will be opened and resealed by the staff responsible for randomization prior to intervention. Subsequently, the tACS experimenter will be informed of the code.

## Assignment of interventions: blinding

### Who will be blinded {17a}

Both participants and clinic staff (including outcome assessors, caregivers, nurses, physical therapists, and statistical analysts) will remain blinded to group allocation until the completion of the study. Only the randomized investigators will have knowledge of the group assignments but will not disclose them to the patients. To ensure double-blinding, patients will be instructed not to discuss their treatment group with other patients or staff members. The disclosure of whether the intervention is tACS or sham-tACS will be withheld throughout the study.

### Procedure for unblinding if needed {17b}

When encountering serious adverse events that necessitate immediate unblinding, the scientific research management department head, data management department project leader, and statistician will jointly perform the unblinding process and meticulously document it. Unblinding will solely disclose the treatment received by a patient through a randomized number, without impacting the blinding of other participants. It will not be involved in efficacy analyses but will be included in safety analyses.

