## Interventions

### Explanation for the choice of comparators {6b}

The application of tACS as a non-invasive brain stimulation (NIBS) technique in clinical treatment is well-established. In this study, the inclusion of sham-tACS + MIRT in the control group served to elicit a placebo effect, with the only discernible distinction between the tACS + MIRT group and sham-tACS + MIRT being the presence or absence of electrical current. (Further details regarding this intervention can be found in the “Intervention description {11a}” section).

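### Two device letters shared by all patients: for anyone who knows the letters, unblinding one patient reveals the other 59, although the protocol says other participants are unaffected

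*Protocol article*

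**What the plan says.** The section on the two treatment groups under Intervention description {11a} describes the equipment: "This trial utilized two tACS devices, one sham and one active, which were identical in terms of size, color, appearance, weight, and odor". It then fixes the device within patient: "Each participant was consistently assigned to the same device throughout the entire intervention".

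Concealment mechanism {16b} gives the labels, "Both the tACS and sham-tACS devices will have identical appearances and be marked as either A or B", and says that a staff member responsible for randomisation "will inform the tACS experimenter to use either device A or B". The same section expects the operator to be blind: "The tACS experimenter, who administers the intervention, will also remain unaware of the group assignments".

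Procedure for unblinding if needed {17b} applies to serious adverse events that need immediate unblinding. It is carried out jointly by the head of research management, a data management lead and a statistician. The section states: "Unblinding will solely disclose the treatment received by a patient through a randomized number, without impacting the blinding of other participants". Who will be blinded {17a} lists statistical analysts and outcome assessors among those kept blind until the study is complete.

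On the sham, the intervention section says "Sham tACS had no active stimulation", and Explanation for the choice of comparators {6b} describes the only discernible difference between arms as "being the presence or absence of electrical current". The sentence just before the first of these gives 77.5 Hz and 15 mA for true or sham stimulation alike.

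**The concern.** Emergency unblinding harms a trial least when opening one code tells nobody anything about another patient. The protocol claims this property, but a two-letter scheme cannot deliver it to people who hold the letters. The operator is meant to be blind, yet is given the letter for every patient and sees each of them over 20 sessions. Data exported with an A/B group code would put the analyst in the same position.

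The primary outcome, PDQ-39, is answered by the patient, and the comparison is true against sham stimulation. If staff who deal with patients come to know what A and B mean, expectation can reach patients through them. If the analyst knows, analysis decisions are no longer blind. Because the key is shared, one event puts every allocation at risk, including those of patients not yet treated.

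**Working it through.** **Inputs, all from the protocol article**
- Patients: 60. Sample size {14} gives 27 per group, and 27 / (1 − 0.10) = 30 per group, so 2 × 30 = 60. The attrition step reproduces. It matters here only as the source of the 60.
- Devices: 2, one active and one sham ({11a}).
- Labels: A and B ({16b}).
- Device within patient: constant over all 20 sessions ({11a}).
- Person told each patient's letter: the tACS experimenter ({16b}, {16c}).

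**Step 1: size of the key.** With two devices and two labels there are only two possible keys: A active and B sham, or the reverse. One correct fact about one patient settles which.

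**Step 2: what one disclosure reveals.** Suppose an observer knows the letters of m patients and learns the treatment of one of them. The key is then fixed, and the other m − 1 allocations follow with certainty.
- Observer who knows all letters: 60 − 1 = 59 of the other 59.
- Operator part-way through, for example with 20 patients treated (illustrative): 20 − 1 = 19 at once, then the remaining 60 − 20 = 40 as each letter is given. In total 19 + 40 = 59.
- Observer who knows no letters: 0 of 59.

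**Step 3: what {17b} implies.** 0 of 59 for everyone. This is true only for the last type of observer.

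**Step 4: participant-specific codes.** With 60 codes and no visible letter, opening one code determines 0 of the other 59. If the arms were forced to exactly 30 and 30, the chance that any other patient shares the opened patient's arm is 29/59 = 0.49, so almost nothing is learned.

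**Step 5: the roles side by side.** {17b} has a statistician take part in unblinding, while {17a} keeps statistical analysts blind. The article does not say whether these are different people. If they are the same person and the data carry the letters, Step 2 applies with m = 60.

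**The case against.** The strongest reply is that the exposed audience is small. {17b} works through the patient's randomisation number and names three management or statistical roles. It does not say that the result goes to the experimenter, who is the only role the text describes as being told letters. Data collection {18a} has outcomes assessed by raters unaware of treatment, and nothing says that the experimenter rates anything. Formal unblinding is reserved for serious adverse events that need it at once, so it may never happen. This all stands. It limits who is exposed, but it does not make the statement in {17b} true for those who hold the letters.

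A reader might go further and infer that a guess breaks the code as surely as a disclosure, because active patients receive 15 mA and sham patients no current. The documents do not support that. They give no data on how perceptible the current is, and a guess gives a probability rather than the key. They also state safeguards: patients are told not to discuss their group with other patients or staff ({17a}), and to rest and keep talk with staff to a minimum during sessions ({11a}).

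A reader might also want to express the harm in PDQ-39 points. The inputs for that are not in the documents. Moreover, a patient's belief that comes from sensation would be the same under any labelling, so such a figure would not measure this defect.

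The absence of a described blinding check is not a finding in itself, since a journal article may leave it to the full protocol. The sham wording is best read as clumsy: the next sentence and {6b} both say there is no current.

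**Conclusion.** The point holds in a limited form. The containment of unblinding stated in {17b} is incompatible with the two-letter scheme in {11a} and {16b} for anyone who knows the letters. For that person, one disclosure reveals 59 of the other 59 allocations instead of none. This follows from the protocol's own text, assuming only that A and B keep their meaning throughout; the article describes no change of labels.

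It does not show that patients or raters would be unblinded, that unblinding will occur, or that the PDQ-39 comparison is biased by any stated amount. The sample size is unaffected. It is a weakness worth correcting because the stated protection cannot work as written, but it does not invalidate the trial.

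**What to change.** 1. Reconcile {11a}, {16b} and {17b}. For patients still to be treated, use participant-specific codes: randomisation staff select the device and cover its letter, so that the operator sees only the participant's code. Label the analysis data in the same way.
2. If that is not feasible, withhold any emergency-unblinding result from operators, raters and analysts, and reword {17b} to say that other participants stay blinded only with respect to people who do not know the device letters.
3. State that the statistician who takes part in unblinding is not the blinded analyst of {17a}.
4. Add one treatment-guess question for patients and raters at T1 and report the answers descriptively by arm. Do not analyse PDQ-39 by guess: the guess arises after randomisation and can itself be influenced by real benefit, so that analysis could not separate expectation from effect.
5. Reword the sentence in {11a} so that 77.5 Hz and 15 mA are not attributed to sham, in keeping with the next sentence and {6b}.

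Cost: an ethics amendment, one extra question at an existing visit, and more handling by existing randomisation staff. Set-up by those staff at every session would come to at most 60 × 20 = 1,200 sessions if no patient had yet been treated. The true number is lower, because Trial status reports first enrolment in October 2023. Relabelling cannot protect patients already treated, and the article does not say how many remain. Items 2 and 3 still help during the 24-week follow-up.
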